### Data management

The data management of this clinical study will use REDCap™, which is a sophisticated platform that is used to create secure data collection programs and offers an intuitive and comprehensive user interface with a system capable of monitoring and consulting patient records and exporting data for statistical analysis [10]. Although REDCap™ accommodates most clinical research needs, it also offers users the ability to design elaborate and advanced programs [11].

### Statistical considerations

#### Sample size

Considering an expected reduction of two points in the visual analog pain scale (VAS) in 50% of the patients in group B compared to 25% those in group A after surgery with a significance level of 5% and a study power of 80%, and using the Z statistic, where p_1_ (0.5) and p_2_ (0.25) are previously defined, a minimum sample size of 58 patients was obtained, for each of the groups, according to the following formula:
$$ \mathrm{n}={\left( Z\alpha / 2+{Z}_{\beta}\right)}^2\ast \left({p}_1\left( 1-{p}_1\right)+{p}_2\left( 1-{p}_2\right)\right)/{\left({p}_1-{p}_2\right)}^2 $$

Where, Zα/2 is the critical value of the Normal distribution at α/2, i.e., 0.05 and critical value =1.96; Z_β_ is the critical value of the Normal distribution at β, i.e., 0.2 and critical value = 0.84; p_1_ and p_2_ are the previously defined sample proportions of the two groups.

Assuming an alpha of 0.5, a sample size of 58 patients per group was calculated to yield a power of 80% and detect a difference of one point between intervention groups in the 10-point VAS score. Standard differences were estimated to be 1.6 according to previous work (1) and drop-out rates were anticipated to be 28%”.

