### Randomization

Patients who meet the inclusion criteria and have provided informed consent will have their fractures classified according to the system proposed by Magerl et al. The randomization process will be performed for each fracture type (A, B and C). The patients will be randomly allocated into the following two groups: A- conventional open surgery and B- minimally invasive percutaneous surgery. The randomization will be performed via a centralized system. The research team will contact the central randomization system informing the type of fracture (A, B or C). The type of treatment will then be assigned by this system, with the patient being subsequently allocated to the appropriate group. We will use envelopes for each fracture type, following the CONSORT (Consolidated Standards of Reporting Trials) guidelines. The randomization will be performed using numbers generated by a specific software [MedCalc Statistical Software version 18.11.3] and will obey the 1:1 ratio for each group [MedCalc Software bvba, Ostend, Belgium; https://www.medcalc.org; 2019].”general anesthesia. Stability of the spine will be achieved by bilateral short-segment pedicle instrumentation. Pedicle screws will be inserted into the vertebral body one level above and below the fractured vertebra. The fractured vertebra will also be included in the fixation. In the fractured vertebra, a short pedicle screw will be inserted uni- or bilaterally according to the degree of pedicle involvement.

The spine fixation system is composed of a 6.5-mm-diameter polyaxial pedicle screw attached to 5.5 mm rods. The vertebral fixation system will be applied through the conventional open approach in group A (open approach) and percutaneously without open exposition of the injured vertebral segment in group B (minimally invasive percutaneous surgery). Posterior fusion using bone grafts or bone substitutes will not be performed in either group. External immobilization will not be used after surgery, and the patients will be allowed to walk according to their general clinical picture and pain.

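### The 58 per group is not what the printed formula gives (55) and holds no drop-out allowance for the responder comparison, whose power falls from 80% to about 66-68% at the plan's own 28% drop-out

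*Protocol article*

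**What the plan says.** The Sample size section of the protocol article gives two justifications for the same number.

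- **Responder basis.** A two-point VAS reduction is expected "in 50% of the patients in group B compared to 25% those in group A after surgery". The error rates are the usual ones, 5% significance and 80% power. From this, "a minimum sample size of 58 patients was obtained, for each of the groups, according to the following formula". The formula printed is the unpooled one for two proportions. It is annotated with "critical value of the Normal distribution at α/2, i.e., 0.05 and critical value =1.96" for alpha, and the other term "is the critical value of the Normal distribution at β, i.e., 0.2 and critical value = 0.84". Neither the formula nor the paragraph has a drop-out term.
- **Mean-difference basis.** "Assuming an alpha of 0.5, a sample size of 58 patients per group was calculated to yield a power of 80"% for a one-point difference on a 10-point VAS. The variability is given as 1.6, under the label of standard differences, and "drop-out rates were anticipated to be 28"%.

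The Primary outcome subsection of the statistical section names relative risk, absolute risk reduction, risk difference and NNT, which are measures for a binary outcome. The Statistical analysis subsection assigns the chi-square test to proportions and the t test to means.

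**The concern.** Two calculations with different effects, different scales and different treatment of drop-out end at the same 58. If 58 is the number of evaluable patients needed for the responder comparison, any loss takes power below 80%. If 58 already includes the 28% loss, that holds only for the mean difference.

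The responder comparison matches the binary effect measures listed for the primary outcome. If its power is overstated, a relative risk whose interval includes 1 could be read as adequately powered evidence of no difference. The formula, the alpha values and the n also disagree with one another, so a reader cannot tell from the text what 58 represents.

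**Working it through.** **Inputs, all from the Sample size section unless noted:** p1 = 0.50 (group B), p2 = 0.25 (group A); critical values 1.96 and 0.84; mean difference 1 point; 1.6 taken as the SD (an assumption about the label); drop-out 28%. The Randomization section says allocation "will obey the 1:1 ratio for each group".

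**1. The printed formula**

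n = (1.96 + 0.84)² × (0.50×0.50 + 0.25×0.75) / (0.50 − 0.25)²
= 7.84 × 0.4375 / 0.0625 = 54.88, so **55 per group**, not 58.

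**2. Where 58 comes from**

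Pooled variance, with mean proportion 0.375:

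n = (1.96 × √(2×0.375×0.625) + 0.84 × √0.4375)² / 0.0625 = 57.6, so **58 per group**.

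At 58 evaluable per group, power is 80.2% by the pooled normal approximation and 79.9% for the exact power of the uncorrected chi-square test. All of the 80% is used with every patient evaluable, so nothing is left for drop-out.

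**3. The mean-difference basis at alpha 0.05**

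n = 2 × (1.96 + 0.84)² × 1.6² / 1² = 2 × 7.84 × 2.56 = 40.1, so 41 by the normal approximation.

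The t test has 79.8% power at 41 per group and 80.8% at 42. Dividing by 1 − 0.28 gives 41/0.72 = 56.9 and 42/0.72 = 58.3. On this basis 58 does include the 28%.

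**4. Responder power after the stated drop-out**

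58 × 0.72 = 41.76, so 41-42 evaluable per group.

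| Method | 41 per group | 42 per group |
|---|---|---|
| Pooled normal approximation | 65.2% | 66.3% |
| Exact, uncorrected chi-square | 66.6% | 68.4% |
| Unpooled normal approximation | 67.7% | 68.8% |

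To hold 80% after 28% loss, 58/0.72 = 80.6, so 81 per group would have to be randomised.

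**5. The alpha values**

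Taken literally, alpha = 0.5 gives n = 2 × (0.674 + 0.84)² × 2.56 = 11.7, so 12 per group. The paragraph's 58 is reached only with 0.05. In the first paragraph alpha/2 is equated with 0.05, but the critical value 1.96 belongs to 0.025.

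**The case against.** The arithmetic is not in dispute. The objections concern its weight.

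- **The 28% may not apply to the responder endpoint.** That endpoint is defined only as a reduction after surgery. VAS is recorded on the first three postoperative days, when few patients should be lost, as well as out to 24 months. The 28% may describe the two-year follow-up. This stands as a condition on the size: the 66-68% is what follows if the full 28% applies. It does not restore the claim. The section ties the 28% to no time point, and pooled power is about 76% at 10% loss, 73% at 15% and 70% at 20%. Only near-zero loss keeps 80%.
- **Intention to treat keeps everyone.** The principle does not supply missing scores. If drop-outs were counted as non-responders (36% versus 18% of 58), power would be about 59%, which is lower still.
- **55 against 58 is harmless.** Largely accepted. The pooled result suits the planned chi-square test, and 58 errs on the safe side of the printed formula. The mismatch matters because it identifies 58 as an uninflated number.
- **Alpha of 0.5 is an evident misprint.** Accepted. The same section states 5%, and the secondary-endpoints section sets 5% for all analyses. It still needs correcting.
- **Keeping 58 on the mean basis sidesteps the binary measures named for the primary outcome.** This has some force, because the documents do not force that choice. The mean basis is nevertheless legitimate: VAS pain is the stated primary endpoint and a t test is planned for means. Disclosing the responder power stops the shortfall from being hidden.

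**Conclusion.** The concern holds. The 58 cannot give 80% power for both comparisons if the stated drop-out applies to each. With 42 evaluable per group, the responder comparison has about 66% (pooled) to 68% (exact chi-square) power against 80% claimed, so a true 50% versus 25% effect would be missed about one time in three. Across 41-42 per group and all three methods the range is 65-69%. The one-point mean difference keeps about 80%.

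This assumes that the full 28% are lost to the responder analysis, that those patients contribute nothing to it, and that 1.6 is an SD. The drop-out conflict is the substantive error. The wrong formula variant and the two alpha slips are minor, but they should be corrected in the same edit.

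**What to change.** Keep 58 per group and rewrite the Sample size section:

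1. State the basis as two-sided alpha 0.05, a one-point difference in mean VAS, SD 1.6 (labelled as a standard deviation) and about 42 evaluable per group after 28% drop-out, with power of about 80%.
2. State that power for the 50% versus 25% responder comparison is then about 66-68%.
3. Remove the responder calculation as a justification for 58, or print the pooled-variance formula that yields 58 and say that it excludes drop-out.
4. Correct alpha from 0.5 to 0.05, and the value given for alpha/2 from 0.05 to 0.025.

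The cost is rewording and a less favourable power statement for the responder endpoint. No extra patients are needed. If the responder comparison were instead required to keep 80% power after 28% loss, the figure would be 81 randomised per group, which is 23 more per group than planned.

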### Statistical analysis

In the multicenter, randomized clinical trial, comparisons between proportions for the categorical variables will be carried out with the Chi-square test. For verification of differences between measures of central tendency, Student’s t tests for paired samples will be used in the intragroup analysis and for independent samples will be used for the intergroup analysis. In case of comparisons between medians, the Kruskal-Wallis test or another hypothesis test for non-parametric continuous variables will be used.

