### Primary outcome

In the analysis of the results regarding the outcomes, we will employ the relative risk (RR) and its 95% confidence interval (95% CI) and derived estimators, such as relative risk reduction (RRR), absolute risk reduction (ARR), risk difference (RD), number needed to treat (NNT), and number needed to damage (NND), emphasizing that in this clinical trial the intention-to-treat (ITT) principle will be used.. To verify the associations among the other variables, univariate analyses followed by multivariate analyses will be performed through logistic regression, also using RR and its 95% CI as association and magnitude estimators.

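### With 28% drop-out expected and ITT claimed, the named t and chi-square tests, run as written, use only patients scored at the analysed visit and none of the earlier VAS scores

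*Protocol article*

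**What the plan says.** All references are to the protocol article.

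- **Sample size** gives two justifications for the same number. The responder version expects a two-point VAS reduction "in 50% of the patients in group B compared to 25% those in group A after surgery". Its error rates are set conventionally, "with a significance level of 5% and a study power of 80" per cent, and the section states that "a minimum sample size of 58 patients was obtained, for each of the groups". The mean-difference version aims to "detect a difference of one point between intervention groups in the 10-point VAS score" with a standard deviation of 1.6, and adds that "drop-out rates were anticipated to be 28" per cent.
- **Statistical analysis** names the chi-square test for proportions. For means it names a paired t test within groups and a t test that "for independent samples will be used for the intergroup analysis".
- **Primary outcome** (the statistical section) lists RR with its 95% confidence interval, RD, NNT and related measures, "emphasizing that in this clinical trial the intention-to-treat (ITT) principle will be used".
- **Primary outcome measure** has VAS recorded before surgery, on the first three post-operative days, and at 1, 2, 3, 6, 12 and 24 months. No visit is singled out as primary.
- **Secondary endpoints and safety profile** adds adjustment by logistic regression and subgroup analyses. Its open-ended list of factors does not mention baseline VAS.

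**The concern.** The plan expects to lose more than a quarter of its patients, yet the between-arm methods it names are two-sample tests at a single visit. A patient who gives a baseline score and several post-operative scores and then leaves contributes nothing to a t test at a later visit. The scores that say most about that patient's likely later pain are already in the database and go unused.

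Two things are at stake. First, RR, RD and NNT under intention-to-treat need a responder status for every randomised patient, and the absolute measures move with how the missing ones are counted. Second, if patients leave for reasons tied to their earlier pain, and those reasons differ between open and percutaneous surgery, a comparison of attenders alone can be biased. Earlier scores could remove the part of that bias which they explain.

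**Working it through.** **Inputs.** All come from the Sample size section: 58 per arm; responder rates 50% (group B) and 25% (group A); difference 1 point; SD 1.6 (printed as standard differences, read here as SD); drop-out 28%; power 80%. Alpha is taken as two-sided 0.05. The mean-difference paragraph begins "Assuming an alpha of 0.5, a sample size of 58 patients per group", but an alpha of 0.5 would need only 12 per arm, so 0.5 is read as a misprint.

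**Step 1. Reproduce 58.**

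- Mean difference: n = 2(1.96 + 0.84)² × 1.6² / 1² = 2 × 7.84 × 2.56 = 40.1, so 41 per arm. Inflated, 41 / 0.72 = 56.9, so 57. An exact t-test calculation needs 42, and 42 / 0.72 = 58.3. The stated 58 agrees to rounding. In the other direction, 58 × 0.72 = 41.8, and 42 per arm gives about 81% power. This sizing therefore counts on about 42 scored patients per arm.
- Responders: the two-sided pooled-variance formula for 50% against 25% gives 58 with no allowance for loss. (The unpooled formula as printed gives 54.9, so 55.) Whether the responder sizing should carry an allowance is a separate question.

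**Step 2. Patients without a value.** 58 × 0.28 = 16.2 per arm. This is an upper figure, because it applies the whole 28% at the visit analysed. The article ties the 28% to no visit. If a score from days 1 to 3 were primary, the loss could be close to zero. The range is 0 to about 16 per arm.

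**Step 3. Effect on the responder measures.** With missing scored as non-response, the rate in each arm is p × (1 − loss). The observed-only row assumes that loss is unrelated to response within each arm.

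| Handling | Group B | Group A | RR | RD (points) | NNT |
|---|---|---|---|---|---|
| Observed only, 28% loss in each arm | 50% | 25% | 2.0 | 25 | 4.0 |
| Missing = non-response, 28% in each arm | 0.50 × 0.72 = 36% | 0.25 × 0.72 = 18% | 2.0 | 18 | 5.6 |
| Missing = non-response, 20% in B, 36% in A | 0.50 × 0.80 = 40% | 0.25 × 0.64 = 16% | 2.5 | 24 | 4.2 |
| Missing = non-response, 36% in B, 20% in A | 0.50 × 0.64 = 32% | 0.25 × 0.80 = 20% | 1.6 | 12 | 8.3 |

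The first two rows use only the article's figures, with the 28% placed at the analysed visit. The 20%/36% split is an assumption that shows how unequal loss would act; it averages 28% but is not in the article. With equal loss the ratio does not move, and only the absolute measures do.

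**Step 4. What the named methods use.** The collected data are one baseline score and up to 3 + 6 = 9 post-operative scores. The independent-samples t test uses one value per patient from one visit. The chi-square test uses one responder status per patient. That status draws on baseline only if the two-point reduction is measured from the pre-operative score, which the article does not say. The paired t test uses two visits, but within a group, so it makes no between-arm comparison. None of these uses a drop-out's intermediate scores.

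**The case against.** The strongest case against is that this is a condensed article and no analysis plan is at hand. A missing-data rule is commonly left to that plan, so its absence here is no fault. That stands, and the point does not rest on it. It rests on what the article does fix: single-visit two-sample tests for an outcome measured up to ten times, with substantial loss expected. An analysis plan that used a longitudinal model would have to depart from the published tests.

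Three stronger readings are tempting, and the documents do not support them.

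- *A reader might infer that the plan can analyse only attenders and so contradicts intention-to-treat.* The article never restricts the analysis to complete cases. RR, RD and NNT can be computed on all randomised patients once a scoring rule is set. Inflating enrolment for expected loss is routine and does not commit the analysis to dropping anyone.
- *A reader might infer that 16 of 58 per arm will have no primary result.* That needs the 28% to apply at the primary visit, and the article fixes neither the timing of the loss nor the primary visit.
- *A reader might infer a sizeable bias.* In simulations with SD 1.6, within-patient correlation 0.6, no true late difference and 28% to 33% loss driven by early pain in opposite directions by arm, the complete-case bias was 0.26 to 0.69 points. Adjusting for the early score cut it to 0.01 or less. That scenario was chosen to be unfavourable and builds in the very dependence that the adjustment removes. It shows that the mechanism exists, not how large the bias would be in this trial.

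It is also fair to say that RR, the estimator listed first, is unchanged by non-response scoring under equal loss, and that a model of mean VAS should not displace the responder comparison on which the trial is first sized. The fix keeps that comparison.

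**Conclusion.** The point holds in a limited form. Run as written, the named between-arm tests use only patients scored at the visit analysed. They do not adjust for baseline VAS and ignore a drop-out's earlier scores, in a trial that expects 28% loss and claims intention-to-treat. If that loss falls equally on both arms at the analysed visit, up to about 16 of 58 per arm lack a value. RD then lies at 25 or 18 points and NNT at 4 or 5.6, depending on whether missing patients are excluded or counted as non-responders; RR is 2.0 either way. If an in-hospital score is primary, the effect could be negligible. Bias in the attenders-only comparison is possible if loss depends on earlier pain differently by arm, but the article gives nothing from which to estimate it. The change is worth making because it uses data already collected; the point does not show that the trial's result would be wrong.

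**What to change.** 1. For the between-arm comparison of mean VAS, replace the independent-samples t test with a likelihood-based repeated-measures model of all post-operative scores. Include baseline VAS, arm, visit and arm-by-visit, and every randomised patient with at least one post-operative score. Report the arm difference at the visit that the plan names as primary.
2. Keep RR, RD and NNT, on all randomised patients. Where responder status is missing, impute it by multiple imputation within arm from baseline and earlier VAS scores.
3. Add one sensitivity analysis that scores missing as non-response.

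No extra patients, visits or measurements are needed. The costs are revised wording, a little more programming, and reliance on missing at random in the main analyses, which the third item probes in one direction only. A patient with no post-operative score adds nothing to the model in item 1 but is still counted in items 2 and 3.

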### Statistical analysis

In the multicenter, randomized clinical trial, comparisons between proportions for the categorical variables will be carried out with the Chi-square test. For verification of differences between measures of central tendency, Student’s t tests for paired samples will be used in the intragroup analysis and for independent samples will be used for the intergroup analysis. In case of comparisons between medians, the Kruskal-Wallis test or another hypothesis test for non-parametric continuous variables will be used.

### Primary outcome

In the analysis of the results regarding the outcomes, we will employ the relative risk (RR) and its 95% confidence interval (95% CI) and derived estimators, such as relative risk reduction (RRR), absolute risk reduction (ARR), risk difference (RD), number needed to treat (NNT), and number needed to damage (NND), emphasizing that in this clinical trial the intention-to-treat (ITT) principle will be used.. To verify the associations among the other variables, univariate analyses followed by multivariate analyses will be performed through logistic regression, also using RR and its 95% CI as association and magnitude estimators.

### Secondary endpoints and safety profile

Considering the secondary outcomes (including minor and major adverse events [AE]), comparing the two groups (A versus B), and for comparing variables between groups A and B, when dealing with proportions, the chi-square test will be used, while for continuous variables the Student’s *t* test (if equal variances) will be used when dealing with averages or the Bonferroni e Benjamini-Hochberg test in the case of medians, in both cases, for independent samples. To minimize the interference of possible confounding variables (in both primary and secondary outcomes), all analyzes will be performed using necessary adjustments such as logistic regression, subgroup analyzes (age, sex, fracture type, duration of surgery, participant center, etc). A significance level of 5% shall be considered in all of the analyses described above.

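### The medians rule names p-value adjustments in place of a test and contradicts the general rule; adjusted relative risks are tied to logistic regression with no conversion from the odds ratio

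*Protocol article*

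**What the plan says.** Two sections of the protocol article give rules for comparing medians.

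- *Statistical analysis*: "In case of comparisons between medians, the Kruskal-Wallis test or another hypothesis test for non-parametric continuous variables will be used".
- *Secondary endpoints and safety profile*: Student's t test for means, or "the Bonferroni e Benjamini-Hochberg test in the case of medians", each applied to independent samples.

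Three statements bear on the relative risk.

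- *Primary outcome* (under the statistical plan), on the outcomes: "we will employ the relative risk (RR) and its 95% confidence interval (95% CI) and derived estimators".
- The same section, on associations among the other variables: "multivariate analyses will be performed through logistic regression, also using RR and its 95% CI as association and magnitude estimators".
- *Secondary endpoints and safety profile*, on confounding in both primary and secondary outcomes: "all analyzes will be performed using necessary adjustments such as logistic regression".

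The planning rates are in *Sample size*: a two-point fall in VAS pain is expected "in 50% of the patients in group B compared to 25% those in group A after surgery". Group B is the percutaneous arm and group A the open arm.

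**The concern.** **Medians.** Bonferroni and Benjamini-Hochberg operate on p-values that some test has already produced. Placed beside the t test as the method for medians in two independent samples, they give the analyst nothing to run. The general section gives a different rule for the same task. Whoever analyses the secondary outcomes must decide which section governs, and should not be making that choice after seeing the data.

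**Relative risk.** A logistic model estimates log odds, so its exponentiated coefficient is an OR. The OR approximates the RR only when events are uncommon, and the pain responder rates planned here are 25% and 50%. If the coefficient were reported under the RR label that the protocol asks for, the adjusted effect would look considerably larger than it is and would disagree with the unadjusted RR in the same report.

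**Working it through.** **1. Planning rates.** From *Sample size*: p1 = 0.50 (group B), p2 = 0.25 (group A), two-sided 5% level, 80% power, 58 per group. The pooled-variance formula, with mean proportion 0.375, reproduces that number:

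n = [1.96 × √(2 × 0.375 × 0.625) + 0.84 × √(0.25 + 0.1875)]² / 0.25² = (1.342 + 0.556)² / 0.0625 ≈ 57.6, so 58.

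The unpooled formula as printed gives 2.80² × 0.4375 / 0.0625 = 54.88, so 55. That is a separate matter. Nothing below depends on it; it matters here only that 50% and 25% are the rates behind the design.

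**2. RR and OR at those rates.**

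- RR = 0.50 / 0.25 = 2.0, a relative increase of 100%.
- OR = (0.50/0.50) / (0.25/0.75) = 1 / 0.333 = 3.0. Read as an RR, this is an increase of 200%.

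**3. The same in whole patients.** Take 29/58 responders against 15/58 (an illustration, since 25% of 58 is 14.5).

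- Exponentiated logistic coefficient: (29/29) / (15/43) = 2.87.
- RR from the table: 29/15 = 1.93.
- Modified Poisson model with robust errors: RR 1.93 (95% CI 1.17 to 3.21).
- Ratio of standardised risks predicted by the logistic model: 1.93.

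A logistic model can therefore lead to a correct RR, but only through a further step.

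**4. Dependence on event rate.** With the RR held at 2:

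| Control rate | OR |
|---|---|
| 5% | 2.11 |
| 10% | 2.25 |
| 25% | 3.00 |
| 40% | 6.00 |

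The gap is small for uncommon complications and large for the pain responder outcome.

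**5. What the two named procedures do.**

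- Input p-values 0.01, 0.02, 0.04.
- Bonferroni multiplies each by 3: 0.03, 0.06, 0.12.
- Benjamini-Hochberg multiplies by 3/1, 3/2 and 3/3: 0.03, 0.03, 0.04.
- A single p-value of 0.03 stays 0.03 under both.

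Patient data enter neither calculation.

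**6. The rank test in the general section.** With two groups, Kruskal-Wallis and the Wilcoxon-Mann-Whitney test (asymptotic, no continuity correction) are the same test. On simulated data with 58 per group, both gave p = 0.536.

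**The case against.** The defence is substantial on scope, and most of it stands.

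- *A reader might infer that medians are left without any test.* The documents do not support that. The general section says "the Kruskal-Wallis test or another hypothesis test for non-parametric continuous variables will be used"; this is workable with two groups and already admits Wilcoxon-Mann-Whitney. The fault is an invalid instruction in one section that contradicts a usable one in another.
- *A reader might infer that logistic regression cannot yield an RR.* It can, by standardising predicted risks. The accurate statement is that the protocol names neither this nor any other route.
- *A reader might infer that the protocol plans to report an OR as an RR.* It says only that RR will be used. Mislabelling is a risk the wording creates, not a stated intention.
- *The sentence joining logistic regression to RR covers the other variables, while the 50% and 25% belong to the pain outcome.* This is correct for that sentence. But the section on secondary endpoints carries logistic adjustment over to the primary outcome, so an adjusted pain estimate is exposed even though that later sentence does not itself mention RR.
- *A reader might add that the t test is faulty because it is conditional on equal variances, or that the secondary p-values will go uncorrected.* Neither is supported. The condition is correctly stated, and the documents give no evidence that variances differ. Naming two adjustment procedures suggests that some correction was meant. What to do when variances differ, and how to handle multiplicity, are details commonly left to an analysis plan.

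The defence does not rescue the two sentences themselves. They pair a procedure with a task it does not perform, or with a measure it does not directly give, and so are more than omitted detail.

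**Conclusion.** Both statements are wrong as written and should be corrected before analysis.

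- **Medians.** The rule for secondary outcomes names p-value adjustments as a two-sample test and conflicts with the general rule. The size of this cannot be expressed as a number: the protocol does not say which outcomes will be summarised by medians. Blood loss, drainage, operating time, hospital stay and fluoroscopy time are plausible candidates, but that is an assumption.
- **Adjusted RR.** If the logistic coefficient were presented as an RR, the planned effect would read 3.0 instead of 2.0. This assumes the planning rates, a model containing treatment alone, and mislabelling of the output. With covariates the figures would shift, and for rare events the discrepancy nearly disappears.

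The unadjusted RR and the absolute measures from the two-by-two table are untouched, as is the sample size.

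**What to change.** 1. In *Secondary endpoints and safety profile*, replace the medians rule with the Wilcoxon-Mann-Whitney test, reported with a Hodges-Lehmann difference and 95% CI. Bring *Statistical analysis* into line by naming the same test; for two groups it is equivalent to the Kruskal-Wallis test already there.
2. Mention Bonferroni or Benjamini-Hochberg only as a multiplicity correction, if one is intended. In that case name one of them and the set of comparisons it covers, since Bonferroni controls the familywise error rate and Benjamini-Hochberg the false discovery rate.
3. For adjusted RRs, name one method: modified Poisson regression with robust errors, log-binomial regression, or standardised risks from the logistic model. Alternatively, keep the logistic model and label its estimate an odds ratio.

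The cost is a few sentences of analysis wording, with no new patients, data or visits. Standardised risks need an interval method, such as the delta method or the bootstrap, to be stated, and log-binomial models can fail to converge, so a fallback should be named if that route is chosen.
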